**Methods:**

Neonates testing HIV positive at birth will be initiated on antiretroviral treatment (ART) and receive an age-appropriate stimulation program, updated at 3 monthly intervals through the first year of life. Neurodevelopment at 12 months of age will be assessed using the Bayley Scales of Infant and Toddler Development, Third Edition (BSID-III). Outcomes will be compared with HIV-infected and HIV-exposed uninfected children (HEU) not having received the stimulatory intervention. Associations between neurodevelopmental outcomes, environmental factors, and parental stress will be investigated. The study will take place at a single site in Johannesburg, South Africa. This non-randomised controlled intervention study, with a single non-blinded comparative intervention group, aims to investigate whether an early childhood stimulation programme used in conjunction with ART initiated at birth can positively impact neurodevelopmental outcomes at 1 year of age in children infected with HIV.

*Trial registration* 15 January 2018, Pan African Clinical Trial Registry PACTR201801002967587

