## Main text

The study is designed as a non-randomised controlled intervention study.

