### Subject selection

Study participants will be recruited from an existing cohort of early-treated HIV-infected and HEU children enrolled onto a clinical trial investigating viral latency and early neonatal provision of anti-retroviral drugs (NCT02431975). Children enrolled and in follow-up in the existing cohort will be offered inclusion into this study, making up the assessment only group. New-born infants will be offered co-enrolment onto the existing study and will make up the group receiving the intervention as well as the assessment. Refusal to participate in one protocol will not jeopardise inclusion onto the other. The trial will be conducted at Rahima Moosa Mother and Child Hospital (RMMCH), Johannesburg, South Africa. The study was approved by the Human Research Ethics Committee of the University of the Witwatersrand (M170653) and registered with the Pan African Clinical Trial Registry (PACTR 201801002967587). Caregiver written informed consent will be obtained.

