### Study procedures

Trained assessors will conduct the BSID-III on children enrolled from the existing cohort at a single time point. Inter-rater reliability of BSID-III administration will be established. Prematurity will be corrected until 24 months chronological age for a gestational age < 37 completed weeks.

The BSID is a direct assessment test using test kit objects to evoke a response. Five developmental domains are evaluated: cognitive, motor, language, social-emotional and adaptive behavior [14]. The BSID have been normed in South Africa [15].

The intervention group will receive a standardised set of developmentally stimulating toys. At three-monthly intervals, additional items will be provided (Table 1).

**Table 1 Tab1:** Items provided to the intervention group through the first year of life

Child’s age	Items provided
Birth	Baby blanket, washcloth, booties and hat, rattle
3 months	Mirror, small ball, book, squeaky toy
6 months	Ring stacker, large ball
9 months	Wooden blocks, stacking cups, book
12 months	Wooden form board, toy car, plastic doll, picture book, crayons and paper

Caregiver information cards developed in South African as part of a developmental activity programme will be provided three-monthly [16]. The card explains what is expected of a child at certain ages in terms of physical, cognitive, language and socio-emotional development. Play ideas and indications of possible developmental delay are included.

BSID-III will be conducted on the intervention group at 12 months of age. The intervention includes visible components—educational toys and parental information cards—and clinic files of these children will be marked to ensure they receive the intervention. Consequently, neither study participants nor assessors are masked to the intervention assignment. Furthermore, by nature of the timing of the assessment conducted at the 12 month follow-up visit the assessor would be able to deduce that the child received the intervention. Assessors have been trained to complete the assessment regardless of exposure to developmental interventions. Baseline comparability in the HIV-infected infants will be established.

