### Data analysis

De-identified data from paper case report forms will be entered into a secure database. Statistical calculations will be performed using SAS version 9.4 (Cary, North Carolina, USA). Anthropometric Z-scores will be calculated using WHO software [23]. P-values will be two-tailed and p-values < 0.05 will be considered statistically significant.

Descriptive statistics will describe the characteristics of the early-treated perinatally HIV-infected children enrolled in the existing cohort in terms of demographics, growth parameters, and HIV-related factors. Composite cognitive, language and motor scores will be described. Continuous variables with normal distribution will be described using means and standard deviation with a 95% confidence interval. Frequency tabulations and percentages will be used to describe categorical variables. “At risk” of developmental delay will be defined as any composite score less than 85, and “delayed” as a score less than 70 [24]. Number of children in these two categories will be explored and associations between patient and disease characteristics investigated using the Chi squared test at 5% level of significance. Mean composite scores will be compared between children assessed at 12, 24 or 36 months of age using ANOVA.

Mean composite scores and number of children “at risk” or “delayed” in each subscale will be compared between early-treated HIV-infected and HEU infants assessed at 12 months of age. T tests will compare demographic, clinical and anthropometrical data between groups. The analysis will be expanded to include the HIV-infected infants having received the ECD intervention. The Chi squared test and Kruskall-Wallis 1-way ANOVA will be used to measure variable difference between groups.

Univariate and multiple regression analyses will be performed to establish associations with poor outcomes on the three subscales i.e. composite scores less than 70 or 85. Variables used to establish associations with poor outcomes will include maternal antenatal and postnatal health-related factors, infant birth data, infant health and HIV-related variables, and data pertaining to socioeconomic status and parental stress. Logistic regression will be conducted on various risk factors for each subscale and a score of ≤ 85 will constitute a poor outcome.

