## Limitations

Although comprehensive, the household survey may not include all confounding variables as development is influenced by innumerable factors. Children in the HEU control group would be exposed to the same confounders as the HIV-infected infants. Use of toys and materials is caregiver dependent—children may not be given the intervention in the home environment. Use of the intervention depends on parental acceptance in accordance with cultural norms and child rearing practices. Use of the intervention will be carefully explained to the caregiver and the caregiver will be encouraged to initiate play and interact with her infant. Sufficient time will be allowed for answering questions and repeating explanations. Study attrition will reduce the planned cohort size. Caregivers returning at incorrect study time points will result in children missing the ideal BSID assessment age. The following measures will be undertaken to maintain the cohort in follow-up. Caregivers will be provided with appointment cards for follow-up visits, and study visits will be scheduled for a mutually convenient day. Caregivers will receive a telephone call to remind them of their study visit the day before the visit is due. Visits will be rescheduled if caregivers are unable to honour their appointments. Completion of the assessment depends on the availability of trained assessors. Two assessors have been trained to ensure an assessor is available when scheduling appointments. Assessment bias may occur as assessors have not been blinded to the intervention group; however, assessors have been trained to conduct the assessment in a standardised manner for all participants.

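### The non-randomised intervention contrast is given only unadjusted tests; no covariate-adjusted intervention effect is stated, although suitable covariates are collected

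*Protocol article*

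**What the plan says.** All references are to the protocol article.

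- **Design (Main text).** "The study is designed as a non-randomised controlled intervention study".
- **Controls (Subject selection).** "Children enrolled and in follow-up in the existing cohort will be offered inclusion into this study, making up the assessment only group".
- **Intervention group (Subject selection).** "New-born infants will be offered co-enrolment onto the existing study and will make up the group receiving the intervention".
- **Question (Abstract, Methods).** Whether the programme, given with ART from birth, "can positively impact neurodevelopmental outcomes at 1 year of age in children infected with HIV".
- **Group comparison (Data analysis).** HIV-infected and HEU infants are first compared at 12 months. Then "The analysis will be expanded to include the HIV-infected infants having received the ECD intervention", with chi-squared and Kruskal-Wallis as the named tests.
- **Regression (Data analysis).** Univariate, multiple and logistic regression are planned to find what goes with a low composite score. "Variables used to establish associations with poor outcomes will include maternal antenatal and postnatal health-related factors, infant birth data, infant health and HIV-related variables", and the list ends with socioeconomic status and parental stress.
- **Safeguards.** Study procedures states: "Baseline comparability in the HIV-infected infants will be established". Limitations states: "Children in the HEU control group would be exposed to the same confounders as the HIV-infected infants". Limitations also concedes that the household survey may miss some confounders.

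**The concern.** The contrast that answers the study question is HIV-infected infants with the programme against HIV-infected infants without it. Membership depends on when the child was enrolled and whether the caregiver agreed to take part. Birth characteristics, disease severity, maternal treatment, household circumstances and caregiver commitment could all differ between the two groups and could all relate to the 12-month score.

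The named tests compare raw distributions. If the groups differ at the outset, the difference appears in the result and cannot be told apart from a programme effect. The regression is the one place where covariates enter, but it is aimed at another question and does not list intervention group. An analyst who followed the text as written would finish without an adjusted answer to the main question, although Study measures already provides for birth history, ART history, infant and maternal viral load and CD4, and household data.

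**Working it through.** **1. Does any stated analysis adjust the intervention contrast?**

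| Stated element | Covers intervention vs no intervention in HIV-infected infants? | Adjusts for covariates? |
|---|---|---|
| Chi-squared, Kruskal-Wallis | Yes, as part of a three-group comparison | No |
| Univariate, multiple and logistic regression | Intervention group not listed | Yes, for other questions |
| Baseline comparability | Concerns HIV-infected infants | No; no consequence is stated if the groups differ |
| Shared-confounders sentence in Limitations | No; it concerns HEU vs HIV-infected | No |

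No row has yes in both columns.

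**2. The plan's own power figure.** Sample size gives 45 per group, a difference of 25, SDs of 17 (cognitive), 16 (language) and 20 (motor), and power above 90%. Data analysis gives a two-sided 5% level.

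- SE = SD × √(2/45); power ≈ Φ(25/SE − 1.96).
- Cognitive: SE = 17 × 0.2108 = 3.58; power = Φ(5.02), above 99.99%.
- Language: SE = 3.37; power above 99.99%.
- Motor: SE = 4.22; power = Φ(3.97) = 99.996%.

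The stated figure is reproduced. It says nothing about bias.

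**3. What a bias would do (assumed sizes).** Take no true effect and a confounding bias of b points on the cognitive score. The two-sided rejection probability is 1 − Φ(1.96 − b/SE) + Φ(−1.96 − b/SE), with SE = 3.58.

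One way to obtain b is standardised imbalance × correlation with the score × SD. With 0.3 and 0.3 assumed, one covariate gives 0.3 × 0.3 × 17 = 1.53 points. Two independent covariates acting in the same direction give 3.06, and four give 6.12. The 5-point row is a directly assumed value.

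| Bias b (points) | b/SE | False-positive rate |
|---|---|---|
| 0 | 0 | 5% |
| 1.53 | 0.43 | 7% |
| 3.06 | 0.85 | 14% |
| 5 | 1.40 | 29% |
| 6.12 | 1.71 | 40% |

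At b = 5 the language score (SD 16) gives 32% and the motor score (SD 20) gives 22%.

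**4. What adjustment costs (assumed).** If covariates explain a share R² of group membership, the effective size is 45 × (1 − R²) per group. For R² from 0.1 to 0.3, power for 25 points stays at 99.8% or more on every scale. For an assumed 10-point difference, with no credit for outcome variance that the covariates explain:

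| Scale | Unadjusted | R² = 0.1 | R² = 0.3 |
|---|---|---|---|
| Cognitive | 80% | 75% | 65% |
| Language | 84% | 80% | 70% |
| Motor | 66% | 61% | 51% |

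Any outcome variance that the covariates explain would offset part of this loss.

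**The case against.** The best defence is that this is a condensed article. The regression sentence says what the variables will include, which does not close the list, and an itemised covariate set commonly sits in an analysis plan that is not shown. The non-random design is disclosed, a comparability check is promised, and incomplete measurement of confounders is acknowledged. Both HIV-infected groups come from one site and the same parent trial, and cohort children must be under 36 months, which limits the gap in enrolment period.

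Much of this stands, and it rules out several stronger readings that a reader might infer:

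- **That the plan excludes intervention from the regression, or will never yield an adjusted effect.** The text supports only that intervention is not listed and no adjusted effect is stated.
- **That the trial's error rate is 40%.** That is the top row of an illustration. It needs four assumed confounders that all act in one direction.
- **That comparability will be judged by significance tests.** No method is given. The t-tests in Data analysis follow the HIV-infected versus HEU comparison.
- **That listing parental stress or later infant health is a mistake.** Both are legitimate in a risk-factor model. They would be a problem only in a model meant to estimate the programme's effect.
- **That the shared-confounders sentence is wrong and should go.** It addresses a different contrast, which is itself part of the primary aim.
- **That adjustment is sure to improve precision.** The net effect depends on how strongly the covariates relate both to the score and to group.

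The defence does not remove the core. The article does not leave this analysis to another document. It names the tests for the group comparison and the purpose of the regression, and what it names for the intervention contrast is unadjusted.

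**Conclusion.** The point holds as a choice of analysis that does not fit the design. The intervention contrast is non-randomised, the tests named for it take no covariates, and the regression that does take covariates is a risk-factor model in which intervention group is not listed. The comparability check has no stated consequence, and the shared-confounders sentence does not reach this contrast.

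The size of the harm cannot be derived from the documents. The 7% to 40% range rests on assumed biases of 1.5 to 6 points, SD 17 and 45 per group. It also treats the contrast as a two-group test, whereas the named comparison has three groups including HEU. The control number is a further assumption, because each cohort child is assessed once, at 12, 24 or 36 months, and the number assessed at 12 months is not fixed. What the range shows is that a bias well below the planned 25-point difference would be enough to distort the test.

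Adjustment deals only with measured differences. Enrolment period is almost fully tied to group, so an adjusted result remains an association.

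**What to change.** 1. **Main intervention analysis.** Among HIV-infected infants, fit a linear regression of each 12-month composite score on intervention group, adjusted for a short pre-specified list.
2. **Covariates.** Use variables fixed before the programme starts, for example gestational age or birth weight, age at ART start, first infant viral load or CD4, and maternal antenatal viral load or ART. Add household socioeconomic items that the programme cannot change. The article does not date the survey, so these items should not be assumed to precede the intervention.
3. **Exclusions.** Leave PSI-SF and postnatal growth or viral load out of this model, because the programme may affect them. They may stay in the separate risk-factor model.
4. **Baseline balance.** Report standardised differences. If a t-test were used instead, 45 per group would detect an imbalance of 0.3 SD only about 29% of the time and 0.5 SD about 65%, so a non-significant result would not show comparability.
5. **Limitations.** Keep the shared-confounders sentence, but state that it does not cover the intervention contrast and that enrolment period cannot be adjusted away.
6. **Conclusion.** Word it as an adjusted association.

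The cost is a few degrees of freedom and slightly more analysis work. The covariates come from data that the article already plans to collect.

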### Study measures

Demographic and health-related variables will be collected from the patient’s files for participants enrolled in the existing cohort. Infant data includes birth history; serial anthropometric data; morbidity data; ART history; concurrent medication; immunisations; feeding history; and laboratory data i.e. HIV viral load, HIV total nucleic acid test, CD4 count, and full blood count (FBC). Maternal data consists of: serial anthropometric measurements; ART history; and laboratory data i.e. HIV viral load, CD4 count, and FBC. Permission for data use has been granted by the database holder and site clinical staff are aware of the aims and logistics of the study.

Composite scores for the three developmental subscales of the BSID-III which are administered with direct child interaction—cognitive, motor, and language—will be recorded [14]. Raw scores are converted to scaled scores which are used to derive the composite score for each subscale.

The household survey and the Parenting Stress Index-Short Form (PSI-SF) will be completed with the child’s caregiver. The household survey is a self-styled questionnaire gathering data about the household in which the child lives. Questions cover the following categories: family structure; number of household members diagnosed with HIV; parental nationality; employment; cigarette and alcohol use; water and sanitation measures; type of housing; exposure to sexual abuse and physical violence; childcare arrangements; and access to electricity and basic electronic household items. The household survey consists of a broad set of variables as ECD is influenced both negatively and positively by a myriad of factors [17–19]. The PSI-SF is the condensed version of a self-reported screening tool used to explore parental stress levels associated with parenting children aged 1 month–12 years [20]. Maternal HIV infection can impact parenting skills which in turn influences the child’s wellbeing, ECD and childhood outcomes [21, 22].

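### The environmental and parental-stress associations are modelled only on dichotomised composite scores with an unlimited predictor set; continuous scores should carry the main analysis

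*Protocol article*

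**What the plan says.** The Introduction of the Protocol article gives the group comparison as the primary aim and adds, as a further aim, the associations of neurodevelopmental outcome with environment and parental stress.

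For that further aim the Data analysis section fixes a binary outcome twice:

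- "Univariate and multiple regression analyses will be performed to establish associations with poor outcomes on the three subscales i.e. composite scores less than 70 or" (the second cut-off, 85, closes the sentence).
- "Logistic regression will be conducted on various risk factors for each subscale", where "a score of ≤ 85 will constitute a poor outcome".

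The predictors are given as domains: "Variables used to establish associations with poor outcomes will include maternal antenatal and postnatal health-related factors, infant birth data, infant health and HIV-related variables", followed by socioeconomic and parental-stress data. No number, priority or limit is attached. The Study measures section shows how wide the source data are: "The household survey consists of a broad set of variables as ECD is influenced both negatively and positively by a myriad of factors".

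The same documents treat the score as continuous elsewhere. Study measures records composite scores, and Data analysis compares mean composite scores between ages and between HIV-infected and HIV-exposed uninfected (HEU) infants. Only the association analysis drops the scale.

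**The concern.** A composite score of 84 and one of 55 count as the same outcome at the 85 cut, while 84 and 86 count as opposite outcomes. A graded association with parental stress or household conditions is then harder to detect than it need be.

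Logistic regression adds a second limit: the number of predictors it can carry depends on the rarer of the two outcome classes, not on the number of children. With a small cohort and an unlimited set of risk factors, odds ratios may be imprecise and unstable.

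At stake is an additional aim, not the primary group comparison. The likely harm is moderate associations missed or poorly estimated, although the data to do better are already collected.

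**Working it through.** **Inputs.** From Sample size: 45 in the intervention group and groups of 45 for the power statement; a 25-point difference; SDs 17, 16 and 20; cited scores in HIV-infected infants of 75.89 ± 17.69 (cognitive), 77.18 ± 16.22 (language) and 79.71 ± 20.91 (motor). From Data analysis: cut-offs 70 and 85, two-sided 0.05. The size of the existing cohort and the event rate in early-treated children are not stated, so both are varied below.

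**1. The plan's own figure.** Power = Φ(Δ / [SD·√(2/n)] − 1.96).
- SD 17: 25 / (17·√(2/45)) = 25 / 3.584 = 6.98, so power is above 99.99%.
- SD 16: 25 / 3.373 = 7.41, above 99.99%.
- SD 20: 25 / 4.216 = 5.93, 99.996%.

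The stated figure of more than 90% is reproduced. It concerns a difference between group means. No sample-size reasoning covers the regression.

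**2. Information lost by the cut.** The large-sample efficiency of a binary cut relative to a normal score is φ(z)² / [p(1 − p)], where p is the event rate and z its normal quantile.

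| Event rate | Efficiency | Loss |
|---|---|---|
| 37% | 0.3776² / (0.37 × 0.63) = 0.61 | 39% |
| 50% | 0.3989² / 0.25 = 0.64 | 36% |
| 70% | 0.3477² / (0.70 × 0.30) = 0.58 | 42% |

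The 37% rate corresponds to scores of 90 ± 15 (an assumption): Φ((85 − 90)/15) = 0.369. The 70% rate corresponds to the cited cognitive scores: Φ((85 − 75.89)/17.69) = 0.697. At rarer events the loss grows: efficiency is 0.44 at 16% and 0.34 at 10%.

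**3. The same loss as power.** Illustration: a predictor that splits 90 children into two halves of 45 whose means differ by 11.8 points, SD 17.
- Continuous: 11.8 / 3.584 = 3.29; power 90% (noncentral t, 88 df).
- Cut at 85, lower mean 90: p₁ = Φ(−5/17) = 0.3843 and p₂ = Φ(−16.8/17) = 0.1615, with average 0.2729. Power = Φ{[0.2228 − 1.96·√(2 × 0.2729 × 0.7271 / 45)] / √[(0.2366 + 0.1354)/45]} = Φ(0.0387 / 0.0909) = 66%.
- Cut at 85, lower mean 85: p = 0.500 and 0.244, power 72%.
- Cut at 85, lower mean 76: p = 0.702 and 0.435, power 73%.

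For a 10-point difference, power is 80% as a mean. After the cut it is 58% (upper mean 95) or 54% (upper mean 100). To reach 80% would take 46 per group with the continuous score and 75 to 83 with the cut.

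**4. Events available.** Events = N × rate.
- Lowest case: 45 × 0.10 = 4.5, about 5.
- Highest case: 180 × 0.60 = 108. Here the 72 non-events are the limiting class. The largest limiting class in the whole range is 180 × 0.50 = 90.

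With the cited score distributions, 45 HIV-infected infants give 31 / 31 / 27 events below 85 (cognitive / language / motor) and 14 / 14 / 18 non-events. Adding 45 HEU infants gives 36 / 37 / 28 events among 90. At the 70 cut, 45 HIV-infected infants give 17 / 15 / 14 events.

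Under a rule of thumb of 10 per predictor (an assumption), the limiting class supports between fewer than one predictor (4.5 / 10) and nine (90 / 10).

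**The case against.** The strongest reply is that 70 and 85 are defined categories with a cited source, so modelling them is a legitimate clinical choice for an additional aim, and that predictor selection may be set out in a full protocol or analysis plan not shown. Both points stand. They bear on severity and on how selection is criticised. They do not restore the continuous outcome, because the article itself fixes the binary one.

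A second reply is that group means are already compared on the continuous scale, so the main comparison does not depend on the cut. That is correct. The power figures are therefore an illustration of the loss for a two-level predictor, not the power of any planned test. At the planned 25-point difference both scales have about 100% power, so the loss matters only for more moderate effects.

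Four stronger readings are tempting but not supported:

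- *Univariate screening at 0.05.* The text announces univariate and multiple regression. It does not say that one feeds the other or that a p-value decides entry; 0.05 is the general significance level.
- *Twenty-seven candidates, about one event each.* Study measures can be counted as 11 infant, 5 maternal and 10 household groups plus the Parenting Stress Index-Short Form. That counts data collected. Data analysis names domains and does not say that every item is a candidate or that all enter one model. The number of events is not stated either.
- *Eighty-one tests with about four false positives.* This needs all 27 groups tested singly on three subscales with every null true (27 × 3 × 0.05 = 4.05), which the plan does not set.
- *Most of the information is discarded.* At event rates of 37–70% the loss is about 40%, not more than half.

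**Conclusion.** The point holds as a cheap improvement to an additional aim. The article commits the association analysis to dichotomised scores and an unlimited set of risk factors, and describes no model that uses the continuous score for environment or parental stress.

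The cut at 85 costs about 40% of the information at event rates of 37–70%, enough to take 90% power to about 66–73% in the illustration. This assumes roughly normal scores, SD 17 and two halves of 45.

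The 5 to 108 events per subscale rest on assumed cohort sizes of 45 to 180 and event rates of 10–60%. They show that the number of predictors must be limited, not what the limit is. The primary group comparison is unaffected.

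**What to change.** In Data analysis, make linear regression of the continuous composite score the main association analysis for each of the three subscales. State that the number of predictors will be limited in advance to what the sample supports, once the cohort size is known. Keep the logistic model at the 85 cut-off as a supportive, clinically interpretable analysis with the same limit. Its cut-off wording should be aligned, since the section uses both below 85 and 85 or below.

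Penalised estimation (Firth) for the logistic model is optional, and the choice of predictors is for the investigators. HIV-specific variables such as infant viral load apply only to the infected children, so any model that includes HEU children needs a set that applies to both.

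The cost is slightly more analysis work, and some collected variables will be described rather than modelled. No further data, visits or participants are needed.
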